## Abstract

**Background:**

Rheumatic and musculoskeletal diseases (RMDs) are chronic diseases that may alternate between asymptomatic periods and flares. These conditions require complex treatments and close monitoring by rheumatologists to mitigate their effects and improve the patient’s quality of life. Often, delays in outpatient consultations or the patient’s difficulties in keeping appointments make such close follow-up challenging. For this reason, it is very important to have open communication between patients and health professionals. In this context, implementing telemonitoring in the field of rheumatology has great potential, as it can facilitate the close monitoring of patients with RMDs. The use of these tools helps patients self-manage certain aspects of their disease. This could result in fewer visits to emergency departments and consultations, as well as enable better therapeutic compliance and identification of issues that would otherwise go unnoticed.

**Objective:**

The main objective of this study is to evaluate the implementation of a hybrid care model called the mixed attention model (MAM) in clinical practice and determine whether its implementation improves clinical outcomes compared to conventional follow-up.

**Methods:**

This is a multicenter prospective observational study involving 360 patients with rheumatoid arthritis (RA) and spondylarthritis (SpA) from 5 Spanish hospitals. The patients will be followed up by the MAM protocol, which is a care model that incorporates a digital tool consisting of a mobile app that patients can use at home and professionals can review asynchronously to detect incidents and follow patients' clinical evolution between face-to-face visits. Another group of patients, whose follow-up will be conducted in accordance with a traditional face-to-face care model, will be assessed as the control group. Sociodemographic characteristics, treatments, laboratory parameters, assessment of tender and swollen joints, visual analog scale for pain, and electronic patient-reported outcome (ePRO) reports will be collected for all participants. In the MAM group, these items will be self-assessed via both the mobile app and during face-to-face visits with the rheumatologist, who will do the same for patients included in the traditional care model. The patients will be able to report any incidence related to their disease or treatment through the mobile app.

**Results:**

Participant recruitment began in March 2024 and will continue until December 2024. The follow-up period will be extended by 12 months for all patients. Data collection and analysis are scheduled for completion in December 2025.

**Conclusions:**

This paper aims to provide a detailed description of the development and implementation of a digital solution, specifically an MAM. The goal is to achieve significant economic and psychosocial impact within our health care system by enhancing control over RMDs.

**Trial Registration:**

ClinicalTrials.gov NCT06273306; https://clinicaltrials.gov/ct2/show/NCT06273306

**International Registered Report Identifier (IRRID):**

PRR1-10.2196/55829

## Introduction

### Background

Rheumatic and musculoskeletal diseases (RMDs) are a heterogeneous group of chronic diseases that mainly affect the joints, bones, muscles, tendons, and ligaments, but they can also affect other organs and systems. The growing significance of these diseases stems from their prevalence and their profound impact on the patient’s quality of life. Some examples of RMD are rheumatoid arthritis (RA), with a global prevalence estimated at 0.46% (95% CI 0.39-0.54), and spondyloarthritis (SpA), with a prevalence between 0.2% and 1.6% [1,2].

These diseases are characterized by symptoms including pain or inflammation that may flare up, requiring professional evaluation and treatment modifications. Because these flares may negatively impact a patient's quality of life, it is essential to identify them and act as early as possible. For this reason, closely monitoring the disease and its treatment is important. Sometimes, this follow-up can be hampered by the enormous burden of care and consultation time limitations typical of outpatient settings, as well as by the patients' difficulty in keeping appointments due, in many cases, to work-related reasons or displacements [3]. In addition, the complexity of the treatments administered can lead to doubts regarding dosage and potential contraindications or adverse effects [4-7]. For all these reasons, it is important to maintain open communication channels between patients and professionals to keep everyone informed of incidents in the evolution of the disease and treatment. Telemedicine and digital health thus present a novel opportunity for the clinical management of chronic patients. In this context, implementing telemonitoring in the field of rheumatology has great potential, as it can enable the close monitoring of patients with RMDs [8].

Telemedicine has seen widespread implementation in recent years, not only in rheumatology (as we want to highlight in this protocol) but also in other areas of health care (eg, emergency departments, intensive care units, pharmacies, primary care, etc) [9]. This approach to patient care is endorsed by the World Health Organization (WHO) [10], as increasing scientific evidence shows that it can be a very important channel in patient-physician communication, improving clinical care and aiding in therapeutic decision-making. In fact, it has gained more strength following the COVID pandemic, a time when face-to-face visits to hospitals or health centers were restricted, especially for patients who were more susceptible due to their clinical history [11,12]. Moreover, recently published literature on telemedicine in the context of rheumatology care suggests that telemedicine may be an effective mode of care delivery for diagnosing and managing rheumatic diseases. However, despite these promising results, more studies are still needed to evaluate the effectiveness of this new approach [13,14].

Telemedicine does not necessarily substitute the traditional care model but rather complements it. Both telemedicine and traditional care have their own advantages, and the most effective approach often involves integrating these models to provide comprehensive and patient-centered health care. Telemedicine can complement traditional care by offering additional options for delivering health care services. It provides a means for remote consultations, monitoring, and follow-up care, especially in situations where physical presence is not mandatory. However, for some cases, traditional care models with in-person consultations, diagnostic tests, and procedures may be more appropriate. Therefore, adopting hybrid models that combine in-person and telemedicine services may optimize the strengths of both models and provide a more flexible and adaptive health care system [15,16].

Considering the increasing relevance of telemedicine and the need to continue to provide further evidence, the objectives of this study are outlined in the following section.

### Objectives

The main objective is to evaluate the implementation of a conceptual framework for a hybrid care model called the mixed attention model (MAM) for use in clinical practice.

The secondary objectives are as follows: (1) to identify features associated with adherence to follow-up through the MAM; (2) to evaluate the technological acceptance of the digital solutions included in the MAM; (3) to assess the agreement between patient-reported join assessments and clinician-based join assessments; (4) to evaluate whether the implementation of the MAM improves clinical outcomes compared to conventional follow-up; and (5) to assess patients´ health literacy using a digital interface.

## Methods

### Study Context

Using this framework, we conducted a previous pilot study (Digireuma study) [17] on the needs of patients with RMDs to develop a treatment strategy combining face-to-face visits with telematics follow-up through a mobile health (mHealth) tool. This tool allowed for the monitoring of disease activity, functionality, and overall patient health using electronic patient-reported outcomes (ePROs). Moreover, patients could also report incidents such as flares between their outpatient visits. This pilot study essentially sought to identify unmet needs in the follow-up and treatment of patients with RMDs and redefine the functionalities and features of future versions of this digital tool. During a 3-month follow-up period, patients had the opportunity to complete disease-specific ePROs at a prespecified frequency, as well as flare-ups and medication changes at any time. The number of interactions and alerts was assessed. The usability of the mobile solution was measured using the Net Promoter Score (NPS). Following the MAM development, there were 46 patients, 22 with RA (48%) and 24 (52%) with SpA). There were a total of 4019 interactions in the RA group and 3160 in the SpA group. A total of 15 patients generated a total of 26 alerts, of which the majority were managed remotely. In terms of patient satisfaction, 65% of respondents were considered to have approved the mobile solution, resulting in an NPS of 57 and an overall rating of 4.3 out of 5 stars, so we conclude that the use of the digital health solution is feasible in clinical practice to monitor ePROs for RA and SpA. Therefore, these results highlighted the next steps in implementing this telemonitoring method in a multicenter setting.

Accordingly, with the results and feedback obtained from previous experience, we detail the design of a clinical study wherein we will evaluate a new version of our digital health solution for monitoring and treating patients with RA and SpA.

### MAM Explanation

All patients with RMDs treated with biological or targeted disease-modifying antirheumatic drugs (b/ts-DMARDs) are followed up in the immune-mediated disease (IMID) unit. This is a structured care unit comprising a multidisciplinary team of rheumatologists and specialized nurses. All care actions are protocolized, and face-to-face IMID unit visits of patients with RMDS under b/ts-DMARDs are recorded in a database. Based on the objectives described, a theoretical protocol was drawn up on how to implement a mixed model combining face-to-face visits with telematic follow-up. The MAM protocol [17] is a care model that incorporates a digital mobile app that patients can use at home and professionals can review asynchronously to detect incidents and monitor clinical evolution between face-to-face visits (Figure 1 depicts a flowchart escribing the participant inclusion in the study and subsequent steps). This protocol considers the role of each of the professionals in the unit, how face-to-face and telematic follow-up is carried out, and how to act according to the response to prescribed treatment.

**Figure 1 figure1:**
[figure not shown]
Flowchart describing the inclusion in the study and the different steps according to the timetable established for the face-to-face and digital visits. ePRO: electronic patient-reported outcome; IC: informed consent; RA: rheumatoid arthritis; SpA: spondyloarthritis.

### Development of the Digital Health Solution

A survey of health professionals and patients was carried out with the aim of identifying their needs and preferences regarding digital health as applied to rheumatology. Questions queried patients' familiarity with telemonitoring tools and mobile apps, the ease with which they could contact their rheumatologists, and their preferences and suggestions about the features that a digital solution should include. As for the professionals, they responded to a survey on the use of telemonitoring tools in clinical practice, training in the subject, and restrictions that hinder a wider implementation of telemedicine.

Combining this information and following a team-based approach, the IMIDoc digital health tool was then designed and developed (Figure 2 shows the digital solution outline). Throughout the process, clinical, technical, and biomedical researchers and patient teams participated in a collaborative and interdisciplinary manner. IMIDoc is based on the MAM.

**Figure 2 figure2:**
[figure not shown]
Digital health solution outline. ePRO: electronic patient-reported outcome; RMD: rheumatic and musculoskeletal disease.

The IMIDoc technical platform consists of a mobile app for patients with RA and SpA, a web tool for clinicians, and the back-end infrastructure for data processing and storage. The IMIDoc platform has its own infrastructure to function independently of the hospital information system. Its back-end implementation is deployed in the cloud with a service-based technology approach that provides support to the IMIDoc mobile app and clinical tool.

The IMIDoc mobile app has been developed for both Android and iOS platforms and will be available through Google Play and the Apple Store, respectively. This implementation ensures that the app is easily accessible to a wide population of patients and accommodates various smart device preferences. On the other hand, the clinical tool is a web-based application accessible via a link in any standard web browser.

Patients with RA and SpA can record disease-related events and incidents, as well as ePROs, and they can receive messages from rheumatologists and automatic notifications regarding pending tasks and educational content. Likewise, rheumatologists can access the information recorded by patients through a web application. This enables clinicians to monitor and track the disease and contact patients to address any issues remotely.

### Study Design

#### Overview

This is a multicenter prospective observational study involving 360 patients with RA and SpA from 5 Spanish Hospitals: Hospital Universitario La Paz (HULP), Hospital Universitario Vall d´Hebron (HUVH), Hospital Universitario Bellvitge (HUB), Hospital Universitario Infanta Leonor (HUIL), and Hospital Universitario Ramón y Cajal (HURyC).

#### Participants

A total of 360 patients will be enrolled in the clinical study, comprising the group receiving MAM intervention and the control group, following the traditional care model matched by age and sex (Table 1). The inclusion criteria for patients in the MAM group are as follows: (1) adult patients >18 years; (2) patients with RA or SpA under treatment with b/tsDMARDs followed in the complex therapy unit (CTU); and (3) patients with an available smartphone. The exclusion criterion includes patients with conditions that hinder or prevent the use of a mobile app (eg, blindness, developmental delay, dementia, and digital illiteracy).

**Table 1 table1:** Patients at each hospital treated with the MAM^a^ or a traditional care model.

Hospital	Patients in the MAM (n=280), n			Patients in the traditional care model (n=80), n	
	RA^b^	SpA^c^	RA		SpA
HULP^d^	40	40	10		10
HURyC^e^	30	30	10		10
HUVH^f^	30	30	10		10
HUIL^g^	20	20	5		5
HUB^h^	20	20	5		5

^a^MAM: mixed attention model.

^b^RA: rheumatoid arthritis.

^c^SpA: spondylarthritis.

^d^HULP: Hospital Universitario La Paz.

^e^HURyC: Hospital Universitario Ramón y Cajal.

^f^HUVH: Hospital Universitario Vall.

^g^HUIL: Hospital Universitario Infanta Leonor.

^h^HUB: Hospital Universitario Bellvitge.

All patients from outpatient consultations treated with b/tsDMARDs for at least 6 months will be invited to participate in the study. Those who have been invited but have declined will be registered, and then if they accept, will be enrolled in the study. The control group will be formed by patients with the same treatments and similar sociodemographic and clinical characteristics.

Due to the exploratory nature of the trial and the fact that the objectives will be measured with different end points, no formal sample size calculation was performed. Based on previous studies in rheumatology comparing clinical parameters using telemonitoring versus conventional monitoring, the number of patients included varied in a wide range (from 44 to 294 patients) [18-20]. The primary end point considered in our study in terms of a 20% reduction in face-to-face visits has not been previously studied, and there is no data in the literature to support the inclusion of a specific number of patients. Therefore, using a crude calculation, we estimated a sample size of 300 patients to be sufficient, considering an infinite population, a confidence level of 95%, a precision of 3%, and an assumption of 15% loss to follow-up. Furthermore, other important aspects to consider in telemonitoring projects with digital health tools are usability and feasibility. Recent studies, similar in objectives to the one proposed here, have included between 40 and 120 patients to evaluate the usability and feasibility of telemedicine applications and systems in RMDs [21]. As for the usability evaluation of the clinical tool discussed in this paper, the study is designed as a multicenter initiative, anticipating the participation of at least 10 health care professionals or digital clinicians. Considering the factors mentioned earlier and the expertise of these users within the field, we contend that this participant count is sufficient for the intended evaluation.

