##### Digital Variables and ePROS

For RA patients, the variables include self-assessed tender joint count (sTJC), self-assessed swollen joint count (sSJC), and SDAI. DAS28 will be calculated and managed as patient-derived DAS28 (PtDAS28) and HAQ. Finally, in patients with SpA, the variables include sTJC, sSJC, BASDAI, BASFI, and ASAS-HI.

Health care resource utilization will be documented, including the number of outpatient consultations, emergency visits, drug switches, and nursing and consultant calls. Questions for assessing patient status and treatment tolerance will be recorded. These will include questions such as, “Are you feeling well with the current treatment regimen?” “Have you had symptoms similar to previous outbreaks of your disease?” “If yes, how many outbreaks have you had during the last month?” “Have you experienced any symptoms that you attribute to tolerance problems with the current treatment?” “If yes, please indicate which symptom and to which treatment you attribute it.”
“Have you had any recent fever or infections?” “Have you engaged in any physical activity equivalent to walking for 30 min at least 3 times during the past week?”

To assess the usability of the IMIDoc, questionnaires will collect information regarding willingness, such as the NPS, which evaluates how participants recommend the IMIDo, and follow-up with other patients using the MAM. The System Usability Scale (SUS), consisting of a 10-item questionnaire answered on a scale from 1 to 5 (strongly disagree to strongly agree), will also be used to assess the IMIDoc.

All patients who sign the informed consent form for this project will be invited to participate in a mixed clinical follow-up combining traditional face-to-face visits and home monitoring. The patients will be provided with access to a mobile app that can be downloaded free of charge and that was specially designed in consultation with and under supervision by rheumatologists. The patients will have access to complete questionnaires addressing disease activity, disability, and other domains such as ePROs (Figures 1 and 2). Face-to-face visits will be scheduled at baseline and 6 and 12 months, both for patients included in MAM and for those under the traditional care model.

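### No app-eligibility rule or route of entry is fixed for the 80 controls, so the MAM-versus-control clinical comparison may be selected on digital access or willingness

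*Protocol article*

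**What the plan says.** Under Participants, eligibility is introduced with "The inclusion criteria for patients in the MAM group are as follows"; the list ends with "3) patients with an available smartphone". The next sentence gives the exclusion, "The exclusion criterion includes patients with conditions that hinder or prevent the use of a mobile app", with blindness, developmental delay, dementia and digital illiteracy as examples. It names no group.

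Controls are described twice in the same section. The first description is "following the traditional care model matched by age and sex". The second is "The control group will be formed by patients with the same treatments and similar sociodemographic and clinical characteristics". Table 1 fixes 280 MAM and 80 traditional-care patients by hospital and disease.

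On recruitment, Participants says "All patients from outpatient consultations treated with b/tsDMARDs for at least 6 months will be invited to participate in the study". Patients who decline are registered, and are enrolled if they later accept. The last paragraph of Digital Variables and ePROS says "All patients who sign the informed consent form for this project will be invited to participate in a mixed clinical follow-up". Support Resources for Patients makes entry to MAM depend on the patient's agreement. Ethical Considerations requires informed consent from every participant.

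**The concern.** The control group serves the comparison of clinical outcomes with conventional follow-up. This is secondary objective 4 in the Objectives section and part of the main objective in the abstract. It is the study's only controlled clinical comparison.

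If MAM patients must own a smartphone and be able to use an app while controls need not, or if controls are mainly people who were offered the app and refused it, the groups differ from the start in a way that is not measured. Digital access and willingness plausibly go with disease control, engagement with care and treatment adherence. A difference in the proportion in remission or low disease activity could then reflect who entered each group and not what MAM does.

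**Working it through.** **1. Group sizes.** From Table 1, MAM: 2 × (40 + 30 + 30 + 20 + 20) = 280. Control: 2 × (10 + 10 + 10 + 5 + 5) = 80. The total is 360, as stated, and the ratio is 280/80 = 3.5 to 1.

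**2. Does digital eligibility apply to controls?**
- Smartphone: item 3 of a list written for the MAM group. No control list exists.
- App-use exclusion: no group named. It follows directly on the MAM list and is defined by ability to use the app, but it could be read as study-wide. This is unclear, not settled either way.

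**3. How does a patient become a control?**
- All participants consent (Ethical Considerations).
- All who consent are invited to mixed follow-up (Digital Variables and ePROS).
- Entry to MAM depends on agreement (Support Resources for Patients).
- Yet 80 patients are planned for traditional care (Table 1).

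Taken together, a consenting patient reaches traditional care only by refusing MAM or being unable to use it. The text states no other route.

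**4. Can matching or adjustment remove the difference?**
- Matching: age and sex in one sentence; treatment, sociodemographic and clinical similarity in the other. Neither mentions digital access or willingness.
- Baseline data (General Variables): no smartphone, education or digital-literacy item.
- Covariates (Data Analysis): age, sex, concomitant methotrexate, baseline activity, disease duration and smoking, retained only if P<0.1 in univariate analysis. Baseline activity may absorb part of a prognostic difference; the selection itself stays unmeasured.
- Health literacy (objective 5) is assessed through a digital interface, so on its face it would not be captured in controls who do not use the app.

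**5. Which analyses are touched?** Assessment of Primary and Secondary End Points defines the primary end point against each patient's previous year, not against controls. It is untouched. Objective 4 is exposed.

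**6. Illustration of size (assumed inputs only).** The documents give no expected rates. Let a share s of controls be selected on digital access or willingness, with a remission or low-activity rate d points lower than MAM patients, and let MAM have no effect. The spurious difference is s × d. The chance of P<.05 comes from a two-sided two-proportion z test (pooled standard error under the null, 280 versus 80).

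Worked case: base rate 70%, s = 1, d = 10 points, so controls have 60%.
- Pooled rate = (280 × 0.70 + 80 × 0.60)/360 = 0.678.
- Null SE = √[0.678 × 0.322 × (1/280 + 1/80)] = 0.059.
- Actual SE = √[0.70 × 0.30/280 + 0.60 × 0.40/80] = 0.061.
- Chance of P<.05 ≈ 1 − Φ[(1.96 × 0.0592 − 0.10)/0.0612] ≈ 40%.

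| d (points) | s = 1, base 70% | s = 1, base 60% to 80% | s = 0.5, base 70% |
|---|---|---|---|
| 5 | 14% | 13% to 17% | 7% |
| 10 | 40% | 36% to 48% | 14% |
| 15 | 70% | 67% to 78% | 25% |

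The nominal rate is 5%. Both the size and the direction of d are assumptions.

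**The case against.** Several counter-arguments have force.

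- **Decliners.** The text never makes them controls. They are registered and enrolled only if they accept, and someone who refuses the study altogether cannot be a control, since all participants consent. This stands. It does not cover a patient who consents to the study and then declines MAM.
- **The exclusion criterion.** It names no group and may be study-wide. This stands: only the smartphone criterion is expressly limited to MAM.
- **Matching.** The two sentences can be read together, since age and sex are themselves sociodemographic. This stands: they are loose, not contradictory, and the second shows an intent to keep the groups comparable. Neither reaches digital eligibility.
- **The invitation sentence.** It sits in a section on app variables, and its paragraph ends by distinguishing MAM from traditional-care patients, so it may be meant for MAM consenters only. That is a fair reading of intent, but the sentence says all who consent, and no other passage supplies a route to control.
- **Condensed article.** Figure 1, the inclusion flowchart, is not shown, and the full protocol may hold more. That lowers confidence. It does not remove the point, because the article states an eligibility list for one group and an invitation rule for everyone, and these do not fit with 80 planned controls.

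**Conclusion.** The point holds as a risk of selection bias in the between-group comparison of clinical outcomes. The smartphone criterion is MAM-only as written, the reach of the app-use exclusion is unclear, and the consent and invitation statements leave no stated route to the control group other than refusing or being unable to use the app. The planned matching and covariates do not address this.

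A reader might go further and infer that controls will be decliners or digitally excluded patients. The documents do not say so; the source of controls is undefined, and the supported statement is that they may be selected in this way. A reader might also infer that the visit-reduction result is biased. It is not, as written, because its comparator is the previous year.

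The magnitude cannot be derived from the documents. The tabulated figures rest on assumed rates and shares and show only that a moderate gap would matter with 280 versus 80 patients. Confidence is medium. The correction is worth making, but the primary end point does not depend on it.

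**What to change.** 1. Apply the MAM inclusion and exclusion criteria to controls as well: available smartphone, no condition preventing app use, and b/tsDMARD treatment for at least 6 months. The last is already required of everyone invited and needs only to be stated for controls.
2. Restrict the invitation sentence in Digital Variables and ePROS to the MAM group, and state that controls are app-eligible patients of the same hospital and disease, not patients who refused MAM.
3. Replace the two descriptions of the control group with one matching definition. Table 1 already sets hospital and disease; name the remaining variables.
4. Since recruitment was due to start in March 2024, flag any control who was offered and refused MAM, and repeat the clinical comparison without them as a sensitivity analysis.

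The cost is revised wording and a short screening checklist for 80 patients, with slightly slower control recruitment.

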##### General Variables

General variables are those that correspond to clinical records documenting background or baseline information. The following will be collected during baseline visits: demographic variables (sex, age, and BMI); smoking habit; date of diagnosis; serological status for RA, such as rheumatoid factor (RF) anticitrullinated peptide antibodies (ACPA), and histocompatibility antigen (HLA)-B27 for SpA; and treatment information, including start date of current b/tsDMARDs and concomitant therapies such as prednisone, conventional disease-modifying antirheumatic drugs (csDMARDs), and previous treatments.

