### Assessment of Primary and Secondary End Points:

The primary end point will be an at least 20% reduction in face-to-face visits compared to visits carried out in the previous year. This reduction in face-to-face visits will be driven by the number of incidents that can be resolved telematically, the number of total interactions, and the number of ePROS that patients complete during the follow-up period that allows us to assess adherence and telematic monitoring.

The secondary end points will be assessed by tracking the number of accesses and time per access to the digital solution per patient to assess adherence. Agreements between the patients' self-assessment and clinician assessment will be assessed to compare face-to-face visits at 6-month intervals with the closest assessment in the digital solution. We will also measure the proportion of patients in remission or low disease activity according to the activity index every 6 months. Usability and satisfaction perceived by patients will be assessed by the SUS NPS.

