## Results

Recruitment began in March 2024 through initial contacts with patients at the IMID unit, and it will continue until December 2024. The follow-up period will be extended for 12 months for all patients. Data collection and analysis are scheduled for completion in December 2025. The main contribution of this protocol paper is a detailed description of the development of a digital solution to improve and implement an MAM in the field of RMDs.

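### The primary end point looks back a year, but patients may enter after 6 months on a b/tsDMARD, so for recent starters the reference year is not comparable with follow-up

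*Protocol article*

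**What the plan says.** In the protocol article, Participants, the invitation sentence reads: "All patients from outpatient consultations treated with b/tsDMARDs for at least 6 months will be invited to participate in the study". The numbered criteria for the MAM group in the same section ask only for patients "under treatment with b/tsDMARDs followed in the complex therapy unit (CTU" and state no minimum duration.

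Assessment of Primary and Secondary End Points defines the primary end point as "an at least 20% reduction in face-to-face visits compared to visits carried out in the previous year". This is a before-after comparison; the 80 traditional-care patients are not its comparator. On the follow-up side, Results says: "The follow-up period will be extended for 12 months for all patients".

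General Variables lists the "start date of current b/tsDMARDs" and previous treatments among the baseline data. Nothing in the article links these items to the reference year. The candidate covariates in Data Analysis include disease duration but not time on b/tsDMARD.

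**The concern.** The look-back is twice as long as the minimum treatment time. A patient who has been on a b/tsDMARD for 6 to under 12 months brings a reference year made up of some months before treatment, the start itself, and some months on treatment. The follow-up year begins only after at least 6 months of treatment. If visits cluster before and around a treatment start, the count would fall in the next year whatever model of care is used.

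The primary end point is judged against a fixed threshold of 20%, and the plan neither limits the share of recent starters nor adjusts for them. Part of an observed fall could therefore not be attributed to the MAM.

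**Working it through.** **Inputs from the article.** Minimum treatment time at invitation: 6 months (Participants). Reference period: the previous year, taken here as the 12 months before enrolment. Follow-up: 12 months (Results). Target: a fall of 20% (Assessment of Primary and Secondary End Points). The target is stated without a derivation, so there is no figure of the plan's own to reproduce on this point.

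**Inputs that are assumptions.** The article gives none of these:
- k, the visit rate in the affected months divided by the later rate;
- m, the number of reference months affected;
- s, the share of the cohort that are recent starters.

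The later rate is set to 1 for everyone and the MAM effect to zero.

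**Overlap.** 12 - 6 = up to 6 of 12 reference months before treatment.

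**One patient.** Reference-year visits relative to the later rate are 1 + (m/12)(k - 1), so the spurious fall is 1 - 1/[1 + (m/12)(k - 1)]. At exactly 6 months on treatment, m = 6:
- k = 1.25: 1 - 1/1.125 = 11%
- k = 1.5: 1 - 1/1.25 = 20%
- k = 2: 1 - 1/1.5 = 33%
- k = 3: 1 - 1/2 = 50%

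**Cohort.** The spurious fall in total visits is 1 - 1/[1 + s(m/12)(k - 1)]. If recent starters are spread evenly over 6-12 months of treatment, the average overlap is m = 3. If all of them are at 6 months, m = 6.

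| s | k | spread evenly (m = 3) | all at 6 months (m = 6) |
|---|---|---|---|
| 10% | 1.5 | 1.2% | 2.4% |
| 10% | 2 | 2.4% | 4.8% |
| 20% | 1.5 | 2.4% | 4.8% |
| 20% | 2 | 4.8% | 9.1% |
| 50% | 1.5 | 5.9% | 11.1% |
| 50% | 2 | 11.1% | 20.0% |

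For example, with s = 50%, k = 2 and m = 3: 1 - 1/(1 + 0.5 × 0.25 × 1) = 1 - 1/1.125 = 11.1%.

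**The opposite case.** MAM Explanation describes a database of face-to-face unit visits by patients on b/tsDMARDs. If the previous-year count came from there, visits before treatment might not be counted at all, which is k = 0 in the same formula. A patient at 6 months would then have a reference count of 1 - 0.5 = 0.5 and show an apparent doubling. For the cohort with m = 3, the reference count is 1 - 0.2 × 0.25 = 0.95 at s = 20% and 1 - 0.5 × 0.25 = 0.875 at s = 50%. The apparent rise is 1/0.95 - 1 = 5% and 1/0.875 - 1 = 14%. Extra visits after the start would offset some of this.

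**No overlap.** With m = 0 the distortion from this source is zero in either direction.

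**The case against.** A reader might infer that the bias can only favour the MAM and could meet the target by itself. The documents do not support that, for four reasons.

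- **Direction.** The article does not say which visits count or where the previous-year number comes from, and the only visit database it describes covers patients on treatment.
- **Follow-up.** The follow-up year is not purely stable treatment. Drug switches are recorded as resource use, and flares, infections and medication problems are recorded as incidents. Both groups also have scheduled visits at baseline, 6 and 12 months, so disease course alone does not set the count.
- **Size.** Six months is a floor, and nothing suggests that as many as 20-50% of patients are recent starters. Placing them all at exactly 6 months roughly doubles the cohort figures.
- **Eligibility.** The two eligibility statements stand in the same section and can be read together, with the invitation sentence supplying the floor. It would overstate the case to say that the plan has no minimum.

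These four points stand, and they limit what can be claimed.

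It can also be said that the study calls itself exploratory and that analysis sets are commonly left to an analysis plan. That does not remove the point. The entry floor and the reference period are both fixed in this article, and it is their combination that makes the comparison unequal, whichever way the bias runs. The controls are described as having the same treatments and similar characteristics, but they do not enter the primary comparison, and treatment duration is not named in how they are chosen.

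**Conclusion.** The concern holds in a limited form. For patients treated for less than 12 months, the reference year and the follow-up year are not like-for-like, and nothing in the article corrects this. A spurious fall in visits is the likely direction, but not a documented one.

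The size depends on assumed values. At cohort level it is about 2-6% (rate ratio 1.5) or 5-11% (rate ratio 2) with 20-50% recent starters spread evenly. It is about double that if all are at 6 months, and only 2-5% if 10% are recent starters, all at 6 months. Against a 20% target this ranges from minor to material. Only in an individual recent starter, or in the most extreme cohort scenario shown, does it reach the target unaided.

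**What to change.** - **Primary visit analysis.** Restrict it to patients whose whole reference year lies on b/tsDMARD treatment. Count any b/tsDMARD, not only the current one, so that long-treated patients who switched are not dropped.
- **Start-up sensitivity analysis.** A patient at just 12 months still has the start inside the reference year. Add a sensitivity analysis that also excludes patients whose start-up period falls there, with the length of that period fixed in advance.
- **All patients.** Show this result as a further sensitivity analysis.
- **Visit source.** State which visits count and where the previous-year number comes from.
- **Controls.** Apply the same rule and the same visit source to the 80 controls, and report the MAM-versus-control difference in change in visits alongside the before-after result.
- **Other end points.** Keep patients treated for 6 to under 12 months in all of them.
- **Eligibility text.** Make the numbered inclusion criteria and the invitation sentence agree.

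The start date of the current drug and the previous treatments are already collected. For switchers, the dates of the earlier b/tsDMARD are also needed, and the article does not name them explicitly. The change is otherwise one of analysis wording and can be made although recruitment has begun. Its cost is some loss of patients, and so of precision, in the primary analysis.
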